## Benefits to Participants

This study has some minimal risks associated with participation and we anticipate that few participants will experience negative events as a result of taking part in the study. This research will improve our understanding of how the enhanced FB-SP model may address SIBs among ALWH. Long-term, supporting ALWH with SIBs through a counseling intervention carried out by counselors is expected to reduce SIBs, improve engagement in HIV-care, and ultimately improve adolescent health and HIV outcomes. Therefore, the risk to individual participants in our study is small and the potential benefit to society is substantial.

## Costs and Compensation

Study participants will receive standard compensation in line with National Health Services Research Committee (NHSRC) and UNC Project Malawi practices for their enrollment visit and research outcome interviews. Namely, participants will receive a travel reimbursement equivalent to 10USD (~17000MK) for their participation.

## Informed Consent

In this study, we are seeking to enroll ALWH 13-19 years to participate. ALWH who are 18 years or older will provide consent for themselves. ALWH 13-17 years will provide assent and will have an authorized adult over 18 years provide consent for them prior to participation. The authorized adult can be a parent, a legal guardian, or someone designated as an authorized representative. The research study will be described briefly to all adolescents accessing ART services at Area 18, Area 25, or Kawale Health Centers in Lilongwe while they wait in the reception area. Once a participant is determined to be eligible for the study a trained interviewer will complete an informed consent process with each participant in their native language, Chichewa. During the informed consent process, the counselor will describe the procedures to be followed, the risks and benefits of participation, the duration of participation, and the steps taken to protect participant’s confidentiality, particularly with respect to keeping all personal and private information (such as HIV, depression status, and SIBs) private to the extent possible by the study team. The counselor will also emphasize that the consent form says that confidentiality of sensitive information cannot be assured during focus groups. Illiterate participants may sign the consent form via thumbprint, in the presence of an impartial witness. Any questions or concerns about privacy will be answered by the counselor or referred to the PI, who will address them. In order to provide protection to this group, we will have rigorous trainings of research staff. We will teach staff to be sure that there is an adequate assessment of understanding. Staff will ensure participants fully understand the content, and time for questions will be encouraged, and answered honestly. We will be clear that refusals will not compromise access to services in any way. We will follow a work practice guideline of when mandatory reporting is required and the best methods to do so, e.g. evidence of exploitation or sexual abuse. Additionally, both sites will adequately map out referrals services to deal with a range of potential needs. All ALWH who screen positive for depression or SIBs will be referred to outpatient psychiatry services that are currently available and staffed by master’s level nursing staff that can prescribe antidepressant medications. ALWH reporting SIBs who choose not to participate will be referred to a mental health provider. Written informed consent will be obtained from each participant and participants will be provided with a copy of their informed consent forms if they are willing to receive it. Study staff will document the informed consent process.

## Adverse Event Reporting

We do not anticipate any adverse events occurring given the nature of the minimal risks associated with this research. However, in the case that a breach of confidentiality does occur, the study team will immediately inform the IRBs. Specifically:

- Deaths related to study participation shall be reported by the PI to the NIMH program officer (PO) immediately and no later than within 5 business days of the PI first learning of the death
- Serious Adverse Events (SAEs) related to study participation shall be reported by the PI to the NIMH PO within 10 business days of the study team becoming aware of the SAE
- Unanticipated Problems Involving Risks to Subjects or Others shall be reported by the PI to the NIMH PO within 10 business days of the study team becoming aware of the problem
- Adverse events and SAEs, including deaths, that are deemed expected and/or unrelated to the study shall be submitted in summary form to the NIMH PO with the annual progress report
- All reported social harms will be documented and communicated to NHSRC and UNC IRB in 7 days
- Protocol violations shall be submitted in summary form to the NIMH PO with the annual progress report
- Suspension or termination of study by IRB shall be reported by the PI to the NIMH PO within 3 business days of receipt

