# METHODOLOGY

## Design of Study

In this randomized controlled pilot trial across five public health clinics, participants will be individually randomized 1:1 either to enhanced FB+SP (N = 30) or augmented usual care (N = 30) and followed for 6 months. Primary and secondary outcomes will be assessed at 2-, 4-, and 6-week; and 3- and 6- month study visits and compared across the two study arms.

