**Box 1: FB+SP Package**

Session 1 (Week 1; 45-60 min)

- SIBs & Suicide Risk Assessment

- Psychoeducation & FB+SP Introduction

- SP activities & Strategy Creation

Sessions 2 (Week 2; 40-45 min)

- SIBs & Suicide Risk Assessment

- SP Check-in & Revision

- FB Problem-Solving Initiation

Sessions 3-6 (Weeks 3-6; 15-20 min)

- SIBs & Suicide Risk Assessment

- SP Check-in & Revision

- FB Problem-Solving Continuation

Concurrent Peer-Support

- 6 group peer-support sessions

- Delivered Monthly

*Optional Ad-hoc Support*

- Telephone/text message check-ins

FB+SP: The FB+SP protocol will embed SP within the existing adolescent-friendly FB model, tailored for the Malawian context.^22,53^ The protocol will include six sessions, starting with the development of the SP during the first session (**Box 1**). Each of the following sessions will include SIBs and suicide risk assessments, SP check-ins and revisions, as well as FB problem-solving to address SIBs and suicide risk (**Box 1**). SP+FB will be delivered by selection of young counselors (mixed genders, aged 20-35) who are motivated to work with young people. Counselors will be trained to deliver non-judgmental counseling that respects the privacy and autonomy of ALWH and enables them to make free and informed choices that are relevant to their individual needs. Training will also include discussion of adolescent development and the unique experiences of ALWH related to stigma, disclosure, social relationship issues, and health care access. Counseling sessions will take place in a youth oriented but discrete location within the HIV clinic and be available on weekends to ensure accessibility.

SP will be initiated on the first session and will consist of an introduction to the program, a SIBs and suicide risk narrative assessment and the co-development of a personalized list of coping strategies. SIBs and suicide risk will continue to be assessed at follow-up sessions, with option telephone and/or text message check-ins.

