FB problem-solving counseling will begin on the second session. The first FB session includes three components called Opening the Mind, Uplifting, and Strengthening, with subsequent sessions building on the first. Opening the Mind refers to the therapeutic process by which, through asking questions, clients are encouraged to open their minds to identify their problems, choose one to work on, identify a feasible solution, and agree on an action plan through an iterative process guided by the counselor. Each structured session lasts 30-45 minutes and will be conducted in a private clinic room in the participant’s local language (Chichewa). No specific retention support will be provided, but participants may identify barriers to engagement in HIV care to address during their counseling session. After 4 sessions of individual therapy, the counselor can refer participants not improving or with suicidal ideation to a supervisor trained in mental health to reassess and manage the case. Case management may include additional counseling or pharmacotherapy, at the discretion of the managing clinician.

Additionally, adolescents will be offered structure peer support via in person group meetings to facilitate engagement in care for ALWH and support SIBS reduction, as is now standard with the existing adolescent-FB package.^53^ Peer supporters will be mature young adults (aged 18-21) who have completed secondary school, are openly living with HIV, and motivated to work with adolescents. The counselors must be willing to maintain participant and colleague confidentiality and sign a confidentiality agreement. Peer Supporters will be trained to deliver youth-friendly group sessions related to HIV care. The content of the 6 peer support sessions includes: Mental Health and HIV, Status Communication, Adherence and Viral Load Testing, Secondary Prevention (Sex and Relationships), Stigma, and Planning for the Future. The 6 sessions will be delivered monthly over 6 months and last 90 minutes each. The group sessions will be in a private space in the clinic in the participant’s local language (Chichewa).

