Augmented usual care: Care for suicidality in public facilities in Malawi includes options for basic supportive counseling by the primary provider or nurse, medication management by the primary provider, referral to the clinic’s psychiatric nurse, or, for acute cases or crises, referral to the psychiatric units at tertiary care hospitals (Bwaila Hospital in Lilongwe District). Nurses and clinicians at the study sites have been specifically trained to use the Tool for Assessment of Suicide Risk for Adolescents (TASR-A) to assess ALWH considered at elevated risk for suicide.^54,55^ For this study, usual care will be augmented by a trained study nurse who will provide mental health evaluation, brief supportive counseling, information, education and support on SIBs, and (if indicated) facilitation of referral to the clinic’s psychiatric nurse or to Bwaila Hospital. The study nurse will have up to 3 follow-up contacts with the participant to assess whether they have followed up on recommended referrals or treatment plans and to assess whether any further outreach is needed.

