# BUDGET

| **Line Item** | **Cost per unit** | **# and type units** | **Cost**  **(USD)** | **Cost (Kwacha)** |
| --- | --- | --- | --- | --- |
| **1. Study Staff** |  |  |  |  |
| Research Assistant | $450 | 2 x 12 months | $10,800.00 | 18,910,800.00 |
| Half-time Research Nurse (SIB management support) following research visits | $450 | 1 x 6 months | $2,700.00 | 4,727,700.00 |
| **2. Compensation for study participants and guardians** | | | | |
| Travel reimbursement for research for participants | $10 | 6 study visits x 60 participants | $3,600.00 | 6,303,600.00 |
| Travel reimbursement for enrollment visit for guardians | $10 | 1 enrollment visit x 60 guardians | $600.00 | 1,050,600.00 |
| Travel reimbursement for counseling & peer support sessions | $5 | 360 Sessions | $1,800.00 | 3,151,800.00 |
| Travel reimbursement for exit interviews | $10 | 10 ALWH & 10 Staff | $200.00 | 350,200.00 |
| **3. Other Research Costs** | | | | |
| HIV Testing | $45 | 2x60 Participants | $5,400.00 | 9,455,400.00 |
| Translation Fees |  |  | $200.00 | 350,200.00 |
| Malawi IRB Fee |  |  | $150.00 | 262,650.00 |
|  | | | | |
| **Total** |  |  | **$25,450.00** | 44,562,950.00 |
| **10% NHSRC fee** |  |  | **$2,545.00** | 4,456,295.00 |
| **GRAND TOTAL (fee included)** |  |  | **$27,995.00** | 49,019,245.00 |

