## Budget Justification (USD)

Personnel

Two Research Assistants in Malawi ($10,800 - 100% effort for 12.0 months) – Two research assistants in Malawi will be hired and trained to assist with the pilot trial.  $450 salary/month x 12 months x 2 research assistants = $10,800

Additionally, we will hire a research nurse half-time to support SIBs management and provide follow-up to ensure appropriate referrals and/or treatment have been implemented. $450 salary/month @ 50% effort x 6 months = $2,700

Total Personnel Costs $ 13,500.

Compensation for Study Participants and Guardians

Travel Reimbursement for study visits for participants ($3,600) – A total of 60 participants will be included in our proposed aims. Each participant will receive $10 per study visit (6 per participant) for travel reimbursement.

Travel Reimbursement for enrollment visit for guardians ($600) – Each guardian (for 60 adolescent participants aged 13-19) will receive $10 for travel reimbursement for the initial enrollment visit.

Travel Reimbursement for counseling/peer support sessions for participants ($1,800) – Each participant will receive $5 for travel reimbursement for each counseling or peer support session. 30 participants will receive 6 counseling sessions and 6 peer support sessions (12 sessions total).

Travel Reimbursement for exit interviews ($200) – Each participant will receive $10 for travel reimbursement for each exit interview. 10 adolescent participants and 10 healthcare facility staff will participate in the exit interviews.

Total Compensation for Study Participants and Guardians Costs $ 6,200.00

OTHER RESEARCH COSTS

HIV Testing ($5400) – We will collect viral loads at 45 USD per test for all 60 participants at enrollment and 6 months.

Translation and Transcription Fees ($200) – All study materials including informed consent forms, surveys, and interview guides will be translated into Chichewa, the local language in Lilongwe, Malawi. Translation fees $200.

Malawi IRB Fee ($150) – All research in Malawi must receive ethical approval from the National Health Science Research Committee, which charges a $150 fee to review all applications for ethical approval.

Total Other Research Costs $350

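### Apart from suicidality and partner violence, harms have no common question or schedule, while FB+SP has about twice the scheduled contacts of usual care, so harm counts may be incomplete and not comparable by arm

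*Protocol*

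**What the plan says.** **Reporting.** Section 6.7 (Adverse Event Reporting) sets deadlines for related deaths, related SAEs, unanticipated problems and social harms. Each runs from the moment staff learn of the event or it is reported. A related SAE is "reported by the PI to the NIMH PO within 10 business days of the study team becoming aware of the SAE". For social harms: "All reported social harms will be documented and communicated to NHSRC and UNC IRB in 7 days". Expected or unrelated events go to the funder in an annual summary.

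**Collection.** Table 1 (section 5.6) lists constructs, measures and time points, with no row for adverse events, SAEs, admission, injury or social harm. Section 6.3 promises to monitor social harms closely but names no instrument or visit. It does give two triggers that apply in both arms: SIBs reported at a research assessment, and partner violence reported in a survey section.

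**Contacts.** Participants are randomized to "enhanced FB+SP (N = 30) or augmented usual care (N = 30) and followed for 6 months". Research visits are the same in both arms; the budget has "6 study visits x 60 participants", that is, baseline plus FU1 to FU5. FB+SP adds individual counselling ("The protocol will include six sessions, starting with the development of the SP during the first session") and peer groups ("The 6 sessions will be delivered monthly over 6 months and last 90 minutes each"). Under augmented usual care (section 5.1) a study nurse gives an evaluation, and then "The study nurse will have up to 3 follow-up contacts with the participant".

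**The concern.** If no one asks a fixed question at a fixed visit, an event is recorded only when some contact happens to bring it out. The number of contacts is set by randomized arm. Two things follow. Harms may be under-recorded overall, and more so in the arm that is seen less. Any tabulation by arm would also mix harm with frequency of contact.

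This matters because the participants are 13 to 19 years old with current or past SIBs, because section 6.7 requires summaries to the funder, and because the pilot is meant to inform a later trial. Unwanted disclosure is a foreseeable harm of group sessions, and no listed assessment asks about it. An analysis plan could not repair this, since it cannot recover events that nobody asked about.

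**Working it through.** **1. The plan's own counts.** The budget justification states "30 participants will receive 6 counseling sessions and 6 peer support sessions (12 sessions total"), and 30 × (6 + 6) = 360, which matches the 360 sessions budgeted. Research visits: 6 × 60 = 360, and 360 × $10 = $3,600, also as budgeted. The contact schedule is internally consistent.

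**2. Scheduled contacts per participant after baseline.**

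| | FB+SP | Usual care |
|---|---|---|
| Research visits (weeks 2, 4, 6; months 3, 6) | 5 | 5 |
| Individual counselling (weeks 1–6) | 6 | – |
| Monthly peer groups | 6 | – |
| Nurse follow-ups (maximum) | – | 3 |
| Separate first nurse evaluation (not stated) | – | 0 or 1 |
| Total | 17 | 8 or 9 |

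The ratio is 17/8 = 2.1 or 17/9 = 1.9. Without peer groups it is 11/8 = 1.4, so peer groups supply 6 of the 9 extra contacts (17 − 8). Section 6.3 also offers up to 3 nurse contacts to any participant reporting SIBs. If FB+SP participants use them, the count is 20 against 8, a ratio of 2.5.

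**3. What that could do to recorded harms.** The protocol gives neither the chance that a contact reveals an event nor the timing of nurse contacts, so both are assumed. Events fall evenly over 26 weeks, and each later contact reveals the event with probability p. All contacts are attended. Then

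P(recorded) = average over event time of 1 − (1 − p)^k, with k = number of later contacts.

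Peer groups are placed at equal monthly steps to week 26.

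| p | FB+SP | Usual care, nurse at weeks 1, 2, 4 | Ratio | Usual care, nurse at weeks 2, 9, 17 | Ratio |
|---|---|---|---|---|---|
| 0.1 | 0.437 | 0.195 | 2.23 | 0.257 | 1.70 |
| 0.3 | 0.790 | 0.473 | 1.67 | 0.575 | 1.37 |
| 0.5 | 0.924 | 0.670 | 1.38 | 0.758 | 1.22 |
| 0.8 | 0.992 | 0.889 | 1.12 | 0.923 | 1.07 |
| 1 | 1.000 | 1.000 | 1.00 | 1.000 | 1.00 |

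For illustration, 6 true harms per arm at p = 0.3 with early nurse contacts would be recorded as 6 × 0.790 = 4.7 against 6 × 0.473 = 2.8.

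**4. Dependence on the peer groups.** If peer groups reveal nothing, the ratios at p = 0.1, 0.3 and 0.5 are 1.14, 1.05 and 1.01 with early nurse contacts, and 0.87, 0.86 and 0.90 with spread ones: about 0.9 to 1.1.

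**5. A common source.** Counting only from the five shared research visits gives both arms the same probability (0.46 at p = 0.3, 0.67 at p = 0.5). The ratio is 1.00 if retention, recall and p are equal.

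**The case against.** Several points on the other side stand.

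- Section 6.7 is a reporting clock, and a clock can only start at awareness. The sentence does not itself show how events are sought. The gap shows in what sections 5.6 and 6.3 leave unspecified.
- Table 1 is not a full list of survey content: section 6.3 relies on a partner-violence survey section that has no row there. A harms question could exist on a form not shown. What can be said is that the protocol fixes none.
- A reader might infer that all harms are caught passively. They are not: SIBs, the central harm here, and partner violence have research-assessment triggers in both arms.
- A reader might infer that FB+SP will look more harmful and that control events will be missed. The documents support only that this may happen. The ratio is 1.0 when each contact reveals every event, and an admission or death is more likely than a minor harm to come to light.
- The excess rests on treating a 90-minute peer group as equal to a private interview. With assumed values of 0.5 for research and nurse contacts, 0.3 for counselling and 0.1 for peer groups, and nurse contacts at weeks 2, 6 and 10, detection is 75% against 70%, a ratio of 1.07.
- Section 5.7 plans no by-arm harms comparison, and the summary to the funder is not said to be split by arm, so no stated analysis is biased.
- A reader might also infer that a death in someone who stops attending would be logged only as non-retention. No passage says so, and section 6.7 provides for deaths, including unrelated ones. What is missing is a stated check on those who stop attending.

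None of this supplies a common question or visit for admission, injury, disclosure or other social harm.

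**Conclusion.** The point holds in limited form. Outside SIBs and partner violence, the protocol fixes no common means of finding harms, and scheduled post-baseline contact differs about two-fold by arm (17 against 8 or 9). Under-recording is possible in both arms and more likely in usual care, and harm counts would not be comparable if split by arm. The contact counts come from the documents. The size of any distortion does not: 1.0 to about 2.2 rests on assumed p from 1 down to 0.1, assumed nurse timing, even event times and full attendance, and it largely disappears if peer groups reveal nothing. The change is worth making because it is cheap and because data not collected cannot be recovered later.

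**What to change.** - Add one short, fixed harms checklist to the research assistant survey at FU1 to FU5 in both arms, covering the time since the last visit: admission, injury, violence, unwanted disclosure, other social harm. Give it a row in Table 1.
- For participants who miss FU5, check vital status and admission in the clinic records that section 5.6 already has staff abstract. These two items are not among those listed there, so the abstraction form would need them. The protocol mentions no other tracing contact, so the fix should not depend on one.
- Record the source of each event (research visit, counselling, peer group, nurse, clinic record).
- Base any by-arm count on the common research-visit source. Events learned at sessions are still reported under section 6.7 and are listed separately.

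The cost is one table row, a few minutes at existing visits and two abstraction items, with no extra visits. The survey becomes slightly longer and more events will probably be recorded overall.

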## Study Discontinuation

The study may be discontinued at any time by the University of Pennsylvania IRB, the NHSRC, or other government agencies as part of their duties to ensure that research participants are protected.

## Amendments to Protocol

Should amendments to the protocol be required, the amendments will be originated and documented by the Principal Investigator at UNC and NHSRC. It should also be noted that when an amendment to the protocol substantially alters the study design or the potential risk to the patient, a revised consent form might be required. The written amendment, and if required the amended consent form, must be sent to UNC’s IRB and NHSRC for approval prior to implementation.

## Record Retention

Study documentation includes all report Forms, data collection forms, source documents, Sponsor-Investigator correspondence, and regulatory documents (e.g., protocol and amendments, IRB correspondence and approval, signed patient consent forms). These documents will be retained for 3 years after the completion and final study report.

